## Notes:

## 1. Sample Collection:

- Samples marked with "E" indicate EDTA anticoagulated blood; all others are non-anticoagulated blood.

## 2. Abnormal CK Levels:

- If total creatine kinase (CK) levels are abnormal, additional tests for CK-MB, cardiac troponin, and electrocardiogram (ECG) should be performed at increased frequency, with repeated testing in the short term. The timing of these tests will be determined by the clinical physician.

## 3. Blinding and Unblinding:

- For tests conducted at the NCAIDS laboratory, the specimens must be blinded by the Infectious Diseases Laboratory of Peking Union Medical College Hospital. After testing, the raw results must be returned to the Infectious Diseases Laboratory for unblinding by their personnel.

## 4. HIV Antibody and Nucleic Acid Testing:

- If HIV antibody testing is positive after vaccination, HIV nucleic acid testing must also be performed.

## 5. HIV Antigen-Specific and Neutralizing Antibodies:

- Specimens for HIV antigen-specific antibodies and neutralizing antibodies will be collected at the corresponding time points and tested in a centralized manner.

### 6.4.3 Determination of Success of rTV Vaccination and re-Vaccination

This trial uses the historical response to the Tian Tan strain vaccinia virus as a reference for the expected response following rTV vaccination.

Based on smallpox vaccination experience, first-time vaccine recipients typically exhibit a progression of skin reactions at the vaccination site, including papules, vesicles, pustules, scabs, and scab shedding, which generally takes about 3 weeks (see Appendix 6 for details). In individuals revaccinated with vaccinia virus, successful vaccination also follows this progression but with milder reactions and a shorter duration. For the rTV vaccine, the insertion of the HIV gene has significantly reduced the virulence of the Tian Tan strain vaccinia virus, and animal studies have shown that the toxicity of the rTV vaccine is 100–1000 times lower than that of the Tian Tan strain vaccinia virus. Therefore, the skin reaction induced by the rTV vaccine in humans may be milder than that of the Tian Tan strain smallpox vaccine. Additionally, due to technical issues, the vaccination site may only show mild needle trauma without the typical pustule formation, indicating vaccination failure.

For these reasons, rTV vaccination is considered unsuccessful if both of the following conditions are met:

1. The vaccination site shows no pustule formation as described above;
2. Serum vaccinia antibodies do not seroconvert (for individuals initially negative for vaccinia antibodies) or show no increase in antibody titer compared to pre-vaccination levels (for individuals initially positive for vaccinia antibodies) two weeks after vaccination.

In the Phase Ib trial, the data management center will unblind the clinical observers (while laboratory personnel remain blinded) on the third day after rTV vaccination to determine whether the rTV vaccination was successful. For individuals with unsuccessful rTV vaccination, a re-administration of the same dose will be performed on the contralateral upper arm four weeks after the first vaccination. Follow-up procedures after re-administration will follow the same protocol as after the initial rTV vaccination.

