The grading of adverse events will be determined after review by the head of the clinical trial unit. The relationship between adverse events and vaccination will be preliminarily assessed by the researchers at the clinical trial unit, but the final determination will be made through discussion between the sponsor and the clinical trial unit and confirmed in writing.

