## 6.9.4 Unblinding

In the Phase Ib trial, participants are enrolled and vaccinated with either the investigational vaccine or placebo under a blinded protocol. On days 3–4 after each rTV vaccination, once all relevant research data have been entered into the database, the blinding will be lifted jointly by the statistician, the principal investigator of the clinical trial, and the sponsor. In the event of a serious adverse event, the principal investigator of the clinical trial will perform an emergency unblinding using the emergency code-break envelope.

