### **6.10.4 Blinding Design**

Given that this trial includes a combined immunization group, a DNA-only group, and a placebo group, a blinded design will be implemented to prevent subjective bias among researchers during vaccination, clinical observation, and laboratory testing. However, since the reactions of participants before and after receiving the rTV vaccine and placebo are noticeably different, the blinding will no longer be effective for participants and clinical observers (but will remain effective for laboratory personnel) 3 days after the rTV vaccination.

In this Phase Ib trial, participants will be vaccinated with either the investigational vaccine or placebo under a blinded protocol. On days 3–4 after the last vaccination in each group, the blinding will be lifted jointly by the statistician, the principal investigator of the clinical trial, and the sponsor.

The blinding process will be carried out by personnel unrelated to the study, with assistance from the statistician, based on the random number table. This includes the preparation of blinded trial materials and emergency code-break envelopes. Each participant will be assigned a unique sequential number, with a corresponding blinded randomization code. After packaging the trial materials, the blinding codes will be stored in duplicate at both the clinical trial site and the sponsor's office.

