### I. General reactions after vaccination

#### (I) Typical local reactions after vaccination

After the successful smallpox vaccination, there are generally papules, blisters, pustules, crusting and scab falling off at the injection site, and also small lesions papules and blisters (called sub-pox) can be seen around the damaged skin, accompanied by localized itching and pain.

Typical local reactions after smallpox vaccination occur at the following time:

| Time After accination | Typical Vaccination Reaction                                                                                                         |
|-----------------------|--------------------------------------------------------------------------------------------------------------------------------------|
| Day 3-4               | A papule appears at the vaccination site.                                                                                            |
| Day 5-6               | The papule develops into a vesicle (blister) with a surrounding red halo, and the top of the vesicle becomes umbilicated (indented). |
| Day 8-9               | The vesicle turns into a pustule, reaching its maximum size between days 8 and 10.                                                   |
| Day 12+               | The pustule gradually dries and scabs begin to form.                                                                                 |
| Day 17-21             | The scab falls off, leaving a permanent scar.                                                                                        |

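### The code break on days 3–4 after rTV comes before either success criterion can be read, and it takes in the sponsor and statistician, to whom the stated reason does not apply

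*Protocol*

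**What the plan says.** Three sections of the protocol deal with breaking the blind after the rTV (or rTV placebo) vaccination.

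- **6.4.3** has the data management center unblind the clinical observers "on the third day after rTV vaccination to determine whether the rTV vaccination was successful". Laboratory personnel stay blinded. The same section calls a vaccination unsuccessful only if no pustule forms and there is also no vaccinia seroconversion or titer rise two weeks after vaccination. Re-administration follows four weeks after the first rTV vaccination.
- **6.9.4** sets the time as "On days 3–4 after each rTV vaccination, once all relevant research data have been entered into the database" and says that "the blinding will be lifted jointly by the statistician, the principal investigator of the clinical trial, and the sponsor".
- **6.10.4** says: "On days 3–4 after the last vaccination in each group, the blinding will be lifted jointly by the statistician", again with the principal investigator and sponsor. Its reason is that, because reactions to rTV and placebo look different, "the blinding will no longer be effective for participants and clinical observers (but will remain effective for laboratory personnel") from 3 days after rTV.

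Annex 6 gives the expected course of the lesion: a papule at day 3–4, a vesicle at day 5–6, and at day 8–9 "The vesicle turns into a pustule, reaching its maximum size between days 8 and 10".

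On causality, 6.5.6 says that after a preliminary assessment at the site "the final determination will be made through discussion between the sponsor and the clinical trial unit". The primary safety endpoints in 6.2.1.1 count grade 3 or higher local and systemic adverse reactions. Section 6.10.5(3) treats adverse reactions as those judged related, possibly related or indeterminable.

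**The concern.** There are two problems.

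First, the purpose given in 6.4.3 does not fit its timing. On day 3 there is no success criterion to judge, and the decision that depends on success is not due until week 4.

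Second, the group that is unblinded is wider than the reason allows. A visible lesion may tell the participant and the examiner which product was given. It tells the sponsor and the statistician nothing, since they do not examine arms. Yet 6.9.4 and 6.10.4 bring both into the code break.

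The sponsor shares the final causality decision, and under 6.2.1.1 relatedness decides whether a grade 3 event counts as a primary safety event. Knowing the arm can shift that judgment. Under 5.3 the statistical office also writes the SAP and runs the analysis, so an unblinded analyst could make analysis choices with the allocation known before lock. The second stage is most exposed. By Table 5 and 6.10.3, the high-dose combined and DNA-only arms receive the same 4 mg DNA schedule and differ only in rTV versus rTV placebo. Their randomized difference therefore begins 3–4 days before the code is opened.

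**Working it through.** **Inputs**
- Code break: day 3 (6.4.3) or days 3–4 (6.9.4, 6.10.4).
- Pustule: day 8–9 (Annex 6).
- Antibody criterion: two weeks, day 14 (6.4.3).
- Re-administration: four weeks, day 28 (6.4.3).
- Follow-up after rTV: 24 weeks (Synopsis).
- Visits after rTV: day 3 and weeks 1, 2, 4, 8, 12, 16, 20 and 24 (6.4.2).
- Diary after rTV: 4 weeks, 28 days (6.5).

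**The protocol's own duration.** Table 5 gives rTV or its placebo at week 14 in the high-dose and DNA-only arms: 14 + 24 = 38 weeks, as stated in 6.4. The low-dose and placebo arms give 12 + 24 = 36, the last column of Table 6. The 24-week figure is consistent.

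**Can success be read at the code break?**

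| Event | Day | Days after a day-3 break | Days after a day-4 break |
|---|---|---|---|
| Pustule | 8–9 | 5–6 | 4–5 |
| Antibody criterion | 14 | 11 | 10 |
| Re-administration | 28 | 25 | 24 |

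Neither criterion can be read on day 3 or 4. The expected finding is a papule, which is not a criterion.

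**How much follow-up comes after the break?** Follow-up is 24 × 7 = 168 days.
- Day 3: (168 − 3)/7 = 23.6 weeks; 165/168 = 98.2%.
- Day 4: (168 − 4)/7 = 23.4 weeks; 164/168 = 97.6%.
- Visits: 9 are scheduled and only the day-3 visit is not after the break, so 8 of 9.
- Diary days: 25/28 = 89% (day 3) or 24/28 = 86% (day 4).

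**The three sections side by side**

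| | 6.4.3 | 6.9.4 | 6.10.4 |
|---|---|---|---|
| Who | Clinical observers, by the data center | Statistician, principal investigator, sponsor | Statistician, principal investigator, sponsor |
| When | Day 3 after rTV | Days 3–4 after each rTV vaccination | Days 3–4 after the last vaccination in each group |
| Reason | To judge success | None; requires entry of relevant data | Visible reactions, for participants and clinical observers |

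No section gives a reason that covers the sponsor or the statistician.

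**The case against.** The strongest reply is that the protocol openly concedes the loss of blinding and that most of it is unavoidable at the site. The Synopsis reports that all 12 Phase Ia subjects showed the expected local reactions to rTV. Section 6.4.3 says that the reaction may be milder than with the parent strain, and milder in people vaccinated before, but that is not evidence of an invisible lesion. This stands. The shares above are calendar counts; they do not measure bias added by the formal code break.

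Other points also stand in part:

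- A reader might infer that no information about the take exists on day 3. Annex 6 does not support that, since a papule, the first step of the reaction, may be visible at day 3–4. What is missing is either of the protocol's criteria.
- Section 6.4.3 can be read as disclosing allocation so that observers can later interpret an absent pustule. That removes the contradiction in wording, but it still does not require day 3.
- A reader might infer that 6.9.4 is impossible to satisfy because it applies "once all relevant research data have been entered into the database". The phrase can mean data up to that point.
- The timings in 6.9.4 and 6.10.4 largely coincide, because rTV or its placebo is the last scheduled vaccination in every arm. They part only for re-vaccinated participants, or if 6.10.4 means the last participant of a group; early participants would then be unblinded later.
- A reader might infer that grading of laboratory events and the immunogenicity results are biased too. Annex 2 grades laboratory values by numeric cut-offs, and laboratory personnel remain blinded.
- Table 3 counts grade 3 or higher adverse events regardless of relatedness, an indeterminate cause counts as related (6.5.6), and the DSMB guides causality of serious events (7.3.1). These limit the effect of a biased causality judgment but do not remove it from the reaction-based endpoints in 6.2.1.1.

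None of this explains why the sponsor and the statistician should be unblinded.

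**Conclusion.** The point holds in a limited form. The code break comes 4–6 days before the expected pustule and 10–11 days before the antibody time point, so it cannot by itself serve the purpose given in 6.4.3. It also reaches the sponsor and statistician without a reason. About 23.5 of 24 weeks of post-rTV follow-up, 8 of 9 visits and 86–89% of diary days come afterwards.

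The stronger reading, that nearly all post-rTV safety data are compromised by the code break, is not supported, because visible lesions would unmask much of the site without it. The avoidable part is the relatedness judgment shared by the sponsor and the analysis choices made before lock. Its size cannot be calculated from the protocol.

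The conclusion assumes that those who lift the blind in 6.9.4 and 6.10.4 thereby learn the allocation, that rTV lesions follow the Annex 6 course, and that the break is timed from each participant's own rTV vaccination. It is worth changing before the trial starts, although in a 36-person study with a mainly descriptive safety evaluation it is not a fatal flaw.

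**What to change.** 1. Reconcile 6.4.3, 6.9.4 and 6.10.4 in one statement of who is unblinded, when and for what purpose.
2. Keep the sponsor staff who judge causality and the analysis statistician blinded until database lock, apart from emergency unblinding. Since 5.3 and 6.10.3 place randomization and analysis in the same office, name separate people for holding the code and for the analysis.
3. Have the data center release allocation to the site only as needed for the existing re-vaccination decision, once the protocol's own success criteria can be read.
4. For events that occur before that release, record the grade and the site's causality assessment before the code is broken.

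The cost is protocol wording and a small data-center procedure. The gain in blinding at the site is limited. The 6 placebo and 6 DNA-only participants (12 of 36) are those expected to have no pustule, so releasing the allocation of participants without one would largely unmask the site by about week 2, and item 4 cannot cover later events. The main gain is with the sponsor and the analyst. No dose, schedule or re-vaccination rule needs to change.

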## 6.5 Evaluation of Vaccine Safety

After each immunization, participants will be observed for 24 hours, during which researchers will closely monitor local and systemic adverse reactions. On vaccination days or follow-up days, researchers will record participants' symptoms, physical signs, and laboratory test results in the raw data forms and transcribe them to the Case Report Forms (CRFs). Participants must complete daily report cards for 2 weeks after DNA vaccination and for 4 weeks after rTV vaccination, and record any abnormalities occurring between follow-up visits on the daily report cards, which will be submitted to researchers at the next follow-up visit (see Appendix 3). During the 2 weeks after DNA vaccination and the 4 weeks after rTV vaccination, participants must also complete a temperature chart for the respective periods. All adverse events occurring between follow-up visits will be recorded in the raw data forms, transcribed to the CRFs, and entered into the database. In cases of discrepancies between the

CRF and the daily report card, the CRF record will take precedence.

### 6.5.1 Evaluation of Local Adverse Events

Local adverse events will be evaluated according to the criteria outlined in Appendix 2, with the following explanations:

1. Pain at the vaccination site: This will be recorded by the participants themselves.
2. Skin erythema, swelling, papules, or induration at the injection site: These will be graded based on the maximum diameter of the reaction and its duration.
3. Blisters or ulcers: These will be graded based on their size, depth, healing time, nature of the blister (e.g., whether it is bloody), duration, and whether necrosis occurs.
4. Pustules: These will be graded based on their size, duration, and whether necrosis occurs.
5. Generalized rash: This will be graded based on the number of papules, presence of itching, exudation, and other characteristics.

### 6.5.2 Evaluation of Systemic Adverse Events

Systemic adverse events will be evaluated according to the criteria outlined in Appendix 2. The evaluation indicators include vital signs such as body temperature, heart rate/rhythm, blood pressure, and respiratory rate, as well as symptoms such as rash, headache, chills/shivering, fatigue/weakness, muscle/joint pain, nausea, vomiting, and diarrhea.

### 6.5.3 Evaluation of Ocular Adverse Events

During the skin reaction period following rTV vaccination, if participants touch the vaccination site or its covering with their hands and then come into contact with their own or others' eyes without proper disinfection, there is a risk of developing vaccinia-related eye diseases (e.g., blepharitis, conjunctivitis, keratitis). If participants or their close contacts experience eye symptoms, they must immediately seek medical attention at the clinical research site. The diagnosis will be recorded in the raw data forms and transcribed to the Case Report Forms (CRFs).

### 6.5.4 Evaluation of Other Clinical Abnormalities

For other adverse events, participants should promptly record the start and end dates of the event, as well as any treatment measures taken, on the daily report card. These events will be graded according to the criteria in Appendix 2. For clinical abnormalities not covered in Appendix 2, the severity will be assessed using the grading standards provided in Table 8.

**Table 8. Criteria on intensity grading of adverse effects**

|                |          |                                                                                                                                           |
|----------------|----------|-------------------------------------------------------------------------------------------------------------------------------------------|
| Grade 1 | Mild     | A discomfort shorter than 48 hours, not requiring medical treatment                                                                       |
| Grade 2 | Moderate | Mild to moderate limitation of daily activities, not requiring or requiring only a little medical intervention                            |
| Grade 3 | Severe   | Significantly restrict daily activities, requiring the care of daily living, requiring medical treatment, and may need to be hospitalized |

---

|                |                  |                                                                                                                                        |
|----------------|------------------|----------------------------------------------------------------------------------------------------------------------------------------|
| Grade 4 | Life-threatening | Extremely restrict daily activities, significantly requiring the care of daily living, requiring medical treatment and hospitalization |
|----------------|------------------|----------------------------------------------------------------------------------------------------------------------------------------|

---

### 6.5.5 Evaluation of Laboratory Test Results

The following tests will be conducted in the laboratory of Peking Union Medical College Hospital, which has passed national quality certification, following standard operating procedures. Abnormal results will be graded according to the criteria in Appendix 2.

1. Hematology tests: Hemoglobin, white blood cell count, and platelet count.
2. Blood biochemistry: ALT, AST, total bilirubin, blood urea nitrogen, creatinine, cardiac enzymes, etc.
3. Urinalysis: Urine protein, urine glucose, and blood cells.

Vaccinia viremia testing will be performed at the NCAIDS Virology and Immunology Laboratory using viral culture methods.

### 6.5.6 Evaluation of the Relationship between Adverse Events and the Investigational Vaccine

Adverse Events (AEs) refer to any unfavorable or unintended experiences that occur in participants during the clinical trial. Serious Adverse Events (SAEs) are those that result in any of the following outcomes:

1. Death;
2. Life-threatening conditions;
3. Hospitalization or prolongation of existing hospitalization (excluding hospitalization due to pre-existing conditions);
4. Persistent or significant disability or incapacity;
5. Congenital anomalies or birth defects (in cases where the participant is pregnant);
6. Other significant medical events (e.g., allergic reactions requiring emergency treatment, seizures not requiring hospitalization or medication, etc.).

Based on the criteria in Appendix 2, participants' systemic and local adverse events, as well as laboratory test abnormalities, will be graded. Social harm should also be classified as an adverse event.

According to their relationship to the investigational product, adverse events can be categorized into one of the following:

1. Definitely unrelated to vaccination;
2. Possibly unrelated to vaccination;
3. Possibly related to vaccination;
4. Definitely related to vaccination;
5. Unable to determine the relationship.

The latter three categories are considered adverse events potentially caused by vaccination and are classified as vaccination-related adverse events. Specific criteria for determining the relationship between adverse events and the investigational vaccine are provided in Table 9.

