**Table 3. Scientific problems to be solved by this phase Ib clinical trial**

| Problems                                                                                                                                                                                     | Primary safety endpoint events                                                                                                                            |
|-----------------------------------------------------------------------------------------------------------------------------------------------------------------------------------------------------|------------------------------------------------------------------------------------------------------------------------------------------------------------------|
| Is a single intramuscular injection of 2 mg or 4 mg of the DNA vaccine safe?                                                                                                                        | The proportion of participants experiencing grade 3 or higher adverse events within 4 weeks after the first vaccination in each group.                           |
| Is it safe to administer three consecutive intramuscular injections of 2 mg or 4 mg of the DNA vaccine?                                                                                             | The proportion of participants experiencing grade 3 or higher adverse events within 4 weeks after each vaccination in each group.                                |
| Is the combined vaccination regimen of three doses of the DNA vaccine at different doses followed by one dose of the replicating recombinant vaccinia virus vaccine safe?                           | The proportion of participants experiencing grade 3 or higher adverse events from the first vaccination until 24 weeks after the last vaccination in each group. |
|                                                                                                                                                                                                     | Primary immunogenicity endpoint events                                                                                                                    |

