#### **6.2.1 Primary Endpoint Events**

##### **6.2.1.1 Primary Safety Endpoint Event**

During the clinical trial, the safety indicators are graded according to Annex 2, and the following are the primary safety endpoint events:

- (1) Grade 3 or higher local adverse reactions;
- (2) Grade 3 or higher systemic adverse reactions;
- (3) Any events of immunization regimen termination caused by vaccine problems;
- (4) Any event leading to the discontinuation of the immunization schedule due to vaccine-related issues.

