## 6.7.2 Early Termination of the Clinical Study

In the low-dose combined immunization group, if three or more vaccine-related adverse events of grade  $\geq 3$  (excluding fever above 39°C for no more than 3 days) occur after each vaccination, the sponsor and the clinical trial unit should terminate subsequent vaccinations for all groups. However, follow-up for the affected participants should continue at least until the adverse events are resolved.

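### Neither definition of the primary safety endpoint counts SAEs, so a vaccination-related SAE graded below 3 that does not stop vaccination can leave the primary proportion at zero

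*Protocol*

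**What the plan says.** Table 3 sets the primary safety endpoint over three windows. The widest is "The proportion of participants experiencing grade 3 or higher adverse events from the first vaccination until 24 weeks after the last vaccination". Grade is the only criterion there.

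Section 6.2.1.1 gives a second definition with four items. Two depend on grade: "Grade 3 or higher local adverse reactions" and "Grade 3 or higher systemic adverse reactions". Two have no grade threshold: "Any events of immunization regimen termination caused by vaccine problems" and "Any event leading to the discontinuation of the immunization schedule due to vaccine-related issues".

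Section 6.5.6 defines an SAE by its outcome. Its sixth category reads "Other significant medical events (e.g., allergic reactions requiring emergency treatment, seizures not requiring hospitalization or medication, etc". Events judged possibly related, definitely related or of undeterminable relationship are all classed as vaccination-related.

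Section 6.5.4 sends any abnormality not covered by Annex 2 to Table 8. Grade 1 there is "A discomfort shorter than 48 hours, not requiring medical treatment". Grade 2 covers mild to moderate limitation of activity with little or no intervention. The Grade 3 description includes a need for medical treatment.

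The secondary endpoints (6.2.2) take in Grade 1 and 2 events within 4 weeks of each vaccination. The halting counts in 6.4.2 and 6.7.2 are also grade-based. In 6.7.2 the wording is "if three or more vaccine-related adverse events of grade" 3 or above, with a fever exception.

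**The concern.** Section 6.2 states that results will be analysed by the frequency of endpoint events, and Table 3 asks whether the full regimen is safe up to 24 weeks after the last vaccination. What counts as an endpoint event therefore decides what the headline safety result can show.

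Seriousness and severity grade are different attributes, and the Protocol rightly keeps them apart. But the primary endpoint uses only grade and schedule termination. An event that the Protocol itself calls serious, and that is judged related to vaccination, can satisfy neither. The primary result for an arm could then read as zero events when a related SAE had occurred in it. With 12 participants per dose subgroup, a single event is a visible part of the result.

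**Working it through.** The Protocol gives no calculated figure to reproduce on this point: the 36 participants are set by regulatory requirement (6.10.2). The allocation is consistent: 12 + 12 + 6 + 6 = 36, and 2:1 of 18 gives 12:6 in each enrolment phase. The check traces one event through the definitions and then sizes the effect.

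**Step 1: which grade.** Take the 6.5.6 example, a seizure needing neither hospitalization nor medication.
- Annex 2 has no seizure row, so 6.5.4 sends it to Table 8.
- It fits Table 8 Grade 1 if it lasts under 48 hours and needs no treatment, or Grade 2 if it limits activity somewhat. Grade 2 also tolerates a little intervention.
- It does not meet Grade 3 as worded.
- If the Annex 2 row for other discomfort were used instead, Grade 3 there involves medication, so the event again falls below 3.

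**Step 2: whether it reaches the primary endpoint.** Section 6.5.8 discontinues immunization for convulsions within 2 hours of a dose, or for a related event of Grade 3 or higher. For other events the next dose is only postponed.

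| Timing of a related seizure SAE, Grade 1 or 2 | Table 3 | Section 6.2.1.1 |
|---|---|---|
| Within 2 hours of a DNA dose | not counted | counted through discontinuation |
| More than 2 hours after a DNA dose, next dose postponed | not counted | not counted |
| After rTV as the last dose | not counted | ordinarily not counted, as no scheduled dose remains |

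**Step 3: whether it reaches the secondary list.** Section 6.2.2 covers 4 weeks after each dose. On the Table 6 schedule (DNA at weeks 0, 4 and 8; rTV at week 12) these windows join up and run from week 0 to week 12 + 4 = 16. Follow-up runs to week 36. A Grade 1 or 2 SAE in the last 36 − 16 = 20 weeks is therefore in neither endpoint list.

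**Step 4: size.** Exact (Clopper-Pearson) 95% intervals, for n = 12 (one dose subgroup) and n = 24 (both combined subgroups, 6.4.2).
- Zero events: the upper limit is 1 − 0.025^(1/n). For n = 12 this is 26.5%; for n = 24 it is 14.2%.
- One event: the lower limit is 1 − 0.975^(1/n), and the upper limit is the 97.5th percentile of a Beta(2, n − 1) distribution.

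| n | SAE not counted | SAE counted |
|---|---|---|
| 12 | 0/12 = 0% (0 to 26.5%) | 1/12 = 8.3% (0.2 to 38.5%) |
| 24 | 0/24 = 0% (0 to 14.2%) | 1/24 = 4.2% (0.1 to 21.1%) |

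The same event adds nothing to the three-event counts in 6.4.2 and 6.7.2.

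**The case against.** The case on the other side is substantial and limits the point in several ways.

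- A reader might infer that the primary endpoint rests on Grade 3 or higher alone. That is true of Table 3 but not of 6.2.1.1, where vaccine-related discontinuation counts at any grade and would catch a convulsion within 2 hours of a DNA dose.
- A reader might infer that the seizure is fixed at Grade 1. It is not. Grade 2 fits equally well, Grade 1 speaks of a mild discomfort, and 6.5.6 leaves the grade to review by the head of the trial unit. What stands is that Grade 3 is not met as worded.
- A reader might point to the neurological complications that Annex 6 places at days 8 to 15. Those are encephalitis and encephalomyelitis. Annex 2 puts post-vaccination encephalitis at Grade 4, and Annex 6 manages encephalomyelitis with intensive care, which fits Table 8 Grade 4. They would be counted, so they do not support this point.
- Most other SAE categories, such as life-threatening events and hospitalization, already map to Grade 3 or 4. The exposed case is narrow.
- The event would not be lost. It is reported within 24 hours (6.5.7), described among adverse events and reactions (6.10.5), and open to the DSMB, which advises on the causality of SAEs and may recommend termination (7.3.1).
- A grade-based halting count and an outcome-based SAE definition can coexist. The texts do not contradict each other in this respect.

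All of this stands. None of it puts a related SAE below Grade 3 into the primary endpoint when vaccination is not stopped.

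**Conclusion.** The point holds in a limited form. Neither definition of the primary safety endpoint counts SAEs, and one of the Protocol's own SAE examples falls below Grade 3 under its own scale. In the timings shown, a vaccination-related SAE can leave the primary proportion at 0/12 instead of 1/12, or at 0/24 instead of 1/24. In the last 20 weeks of follow-up it is also outside the secondary endpoint list.

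This rests on four assumptions: the event is judged vaccination-related; Table 8 is applied as worded; the investigator does not end the schedule because of it; and rTV is the last dose, which a repeat vaccination under 6.4.3 would change. The Protocol gives no probability for such an event, so the intervals show what one event would do and not how likely it is.

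The gap lies in the endpoint definition and not in surveillance. The documents do not support the stronger inference that such an SAE would go unreported. This is a cheap improvement and not a flaw that invalidates the design.

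**What to change.** Add one item to 6.2.1.1 and to the safety endpoints in Table 3: *any vaccination-related SAE, whatever its Annex 2 or Table 8 grade*. Count it in the same participant proportion, in whichever Table 3 window it falls.

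In the same edit, align the two definitions. At present only 6.2.1.1 counts schedule termination, and Table 3 speaks of adverse events where 6.2.1.1 speaks of adverse reactions.

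For the halting counts, 6.4.2 and 6.7.2 should be reconciled with 6.5.6 so that the text says whether a related SAE below Grade 3 counts. Which way that is settled is a clinical matter, and no rule is proposed here.

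The cost is a line of text in each place. SAEs and their relationship to vaccination are already recorded, so no new data are needed. The only downside is that the primary rate may come out slightly less favourable.
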